### Additional research within the project

For the entire GET ON project we will collect cost data, see more details in the VIBRA trial protocol [22] published elsewhere. Specifically, for the HOSENG trial, first, direct costs of the intervention will be assessed: Staff costs (campaign team, VHWs, clinic staff), personnel training costs (VHWs), cost of equipment (HIV tests, consumables, logistics), as well as non-medical costs to the participant (i.e., cost of transportation to the ART service). These data will provide the cost per participant achieving the primary endpoint within 120 days in each cluster arm (“per participant tested cost”). Secondly, a cost-effectiveness analysis will be performed with respect to the primary endpoint. The cost-effectiveness ratio will be presented as incremental cost per additional confirmed HIV test result. Data to assess patient level costs will be collected from a randomly selected sub-sample of study participants from each cluster arm. Costs will be reported in local currencies and US dollars and International dollars. The robustness of results will be tested with probabilistic sensitivity analysis and deriving cost-effectiveness acceptability curves to capture the uncertainty around the probability that the intervention is below the relevant cost-effectiveness thresholds.

A nested study (ADORE study: “ADolescent ORal sElf-testing”) will explore the effectiveness acceptability of oral HIVST among adolescents and young adults with quantitative methods (testing coverage among adolescent and young adults, defined as the proportion of all 12–24-year-old individuals living in a household of the surveyed area with a confirmed HIV test result) and qualitative methods (case-control study). Cases are those who refused testing through oral HIVST and controls are those who accepted testing through oral HIVST. We plan to conduct at least 10 interviews per group, stratified by two pre-defined factors (male vs female; age 12–15 years vs age 16–24 years), following the concept of saturation. Data will be collected by a trained study member, who was part of the HIV-testing campaign, using a piloted interview questionnaire (KoboToolbox; www.kobotoolbox.org), conducted in the local language (Sesotho). Qualitative data will be recorded, transcribed, translated into English and coded and analyzed using the Framework Method [31].

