#### Control clusters

Following standard of care during home-based HIV-testing, every absent household member or those declining HIV-testing will be encouraged to get an HIV test done by the VHW or the nearby health facility. The research team will screen the registers at the health facilities in order to assess if these individuals came for testing in the timeframe of the primary endpoint window.

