### Endpoints

The primary endpoint is HIV-testing coverage among individuals aged 12 years or older in the surveyed area within 120 days after the home visit, defined as the proportion of all individuals aged 12 years or older living in a household of the surveyed area with a confirmed HIV test result.

We define a confirmed HIV-negative result as either being tested HIV-negative as per the algorithm defined in Fig. 2, or being tested HIV-negative within the last 4 weeks with proof of documentation (i.e., documentation in patient’s health booklets). We define a confirmed HIV-positive result as (1) tested HIV-positive as per the algorithm defined in Fig. 2, or (2) being tested HIV-positive but not yet on ART with proof of documentation, or (3) being on ART with proof of documentation.

The rationale for the time point of 120 days is that we leave oral HIVST kits at the households for all absent household members aged 12 years or older who return within a maximum of 3 months (see definition of household member above in the “Procedure” section). An interval of 120 days after home visit allows sufficient time for absent members to return to their households, conduct self-testing, and be followed up by the VHW.

The secondary endpoints are outlined in Table 2.

**Table 2 Tab2:** Secondary endpoints of the HOme-based SElftestiNG (HOSENG) trial

	Endpoint	Definition	Time point following enrollment
1	Testing coverage irrespective of age	Proportion of all individuals living in a household of the surveyed area with a confirmed HIV test result	Within 120 days
2	Blood-based HIV-testing uptake	Proportion of all present individuals living in a household of the surveyed area, being eligible for blood-based HIV-testing and accepting to be tested using blood-based point-of-care HIV test	On the day of the campaign
3	Oral-based HIV-testing uptake	Proportion of all individuals living in a household of the surveyed area for whom an oral HIV self-test (HIVST) was left behind and who performed it	Within 120 days

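### The HOSENG participant cost is defined as travel to ART care, although the costed outcome is a confirmed HIV test result and travel to obtain that result is not named

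*Protocol article*

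**What the plan says.** In the Protocol article, Methods, *Additional research within the project*, the cost paragraph opens with a general pointer: "For the entire GET ON project we will collect cost data, see more details in the VIBRA trial protocol". It then turns to HOSENG specifically and lists direct costs: staff, training of village health workers (VHWs), equipment, "as well as non-medical costs to the participant (i.e., cost of transportation to the ART service".

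The use of the list is stated next: "These data will provide the cost per participant achieving the primary endpoint within 120 days in each cluster arm". For the comparison of arms, "The cost-effectiveness ratio will be presented as incremental cost per additional confirmed HIV test result". Patient-level costs come from a random sub-sample in each arm.

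Under *Endpoints*, the primary endpoint is "defined as the proportion of all individuals aged 12 years or older living in a household of the surveyed area with a confirmed HIV test". One way to count as HIV-positive for it is "3) being on ART with proof of documentation".

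Under *Control clusters*, absent or declining members "will be encouraged to get an HIV test done by the VHW or the nearby health facility", and facility registers are searched for their tests within the endpoint window. The Abstract describes this route simply as referral to a health facility. Under *Intervention clusters*, a reactive self-test is either followed by blood testing by the VHW on the spot or referred to the facility for confirmation.

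**The concern.** The numerator and denominator of the cost measures do not match. The denominator counts people "living in a household of the surveyed area with a confirmed HIV test result". The only participant cost named is travel to ART care, which is not needed to enter that denominator. For a newly diagnosed person, ART care follows the result. Travel that does produce a countable result, in either arm, is not in the list. A control member who goes to the facility and tests negative is counted as an effect, with clinic staff time on the provider side and nothing on the participant side.

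The trial compares a kit left at home with referral elsewhere, so participant travel for testing is one of the costs on which the arms may differ. The Abstract and the Discussion both make the policy message conditional on cost-effectiveness. The planned probabilistic sensitivity analysis varies the inputs that are included and does not restore one that was left out.

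**Working it through.** The article states no cost figure, so there is none to reproduce. The check applies the printed rule to the routes to the endpoint, then derives the error algebraically.

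**Routes to a confirmed result**

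| Route | Travel needed for the result | Travel the printed item names |
|---|---|---|
| Tested at home on campaign day, negative | none | none |
| Control, referred, tests negative at facility | trip to facility | none |
| Intervention, self-test negative at home | none | none |
| Intervention, reactive kit, confirmed at facility | trip to facility | later ART trip, if made |
| Newly positive, confirmed at home or by the VHW on the spot | none | later ART trip, if made |
| Already on ART, documented at the visit | none | ART trips, if counted |

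**Inputs**
- Coverage of 63% (control) and 78% (intervention), from *Sample size*: 78 - 63 = 15 extra results per 100 people.
- Adult HIV prevalence of 17.8% and 26.1%, from *Setting*.
- Not in the document, so assumed: t, the cost of one trip (taken as equal for testing and ART); fC and fI, facility testing trips per 100 people in control and intervention; aC and aI, ART trips per 100 people.

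**Incremental ratio**
- Participant part under the printed rule: t(aI - aC)/15.
- Participant part counting testing travel only: t(fI - fC)/15.
- Error, printed minus testing-travel: t[(aI - aC) + (fC - fI)]/15.

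| fC | fI | aC | aI | Error per extra result |
|---|---|---|---|---|
| 5 | 0 | 1 | 4 | (3 + 5)/15 = +0.53t |
| 5 | 0 | 1 | 1 | (0 + 5)/15 = +0.33t |
| 5 | 3 | 1 | 1.5 | (0.5 + 2)/15 = +0.17t |
| 5 | 5 | 1 | 1 | 0 |
| 1 | 3 | 1 | 1.5 | (0.5 - 2)/15 = -0.10t |
| 1 | 3 | 2 | 1 | (-1 - 2)/15 = -0.20t |

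The ratio is overstated only if (aI - aC) + (fC - fI) is above zero.

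**Ceiling for the ART part.** Suppose all 15 extra results carry the survey prevalence and each positive makes one ART trip. Then 15 x 0.178 = 2.67 and 15 x 0.261 = 3.915 trips; divided by 15, this is +0.18t to +0.26t. Positives already on ART would not add a trip because of the campaign, so the true addition should be lower.

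**Per-arm cost per person tested.** The error is t(a - f) divided by the number covered per 100. In the second row of the table, control is (1 - 5)/63 = -0.06t and intervention is (1 - 0)/78 = +0.01t. An arm's figure is right only if its ART trips happen to equal its facility testing trips.

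**The case against.** The strongest reply is that this is one parenthesis in a condensed article. The cost paragraph defers detail to the VIBRA protocol, which is not shown, and the full cost questionnaire may well ask about testing travel. The article also uses i.e. loosely elsewhere, for example when naming who will collect a sputum sample, so ART travel may be meant as an illustration. The ART service may be the same nearby facility that does the testing.

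Part of this stands: the final costing may differ from the printed item. But the pointer to VIBRA covers cost data for the whole project, and the text then sets out a list specific to HOSENG. The point concerns a definition that is printed, not detail left out. If ART and testing share a building, someone who goes there and tests negative still makes no ART trip.

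Two further replies hold. Travel for testing is not confined to control clusters: intervention members may travel for confirmation, and control members may be tested by the VHW without going to a facility. And ART trips by people already on treatment should roughly cancel between randomised arms, so they distort each arm's cost more than the increment.

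**Conclusion.** The mismatch is real and follows from the text: the participant cost is tied to ART care, while the costed outcome is a confirmed test result. The per-arm cost per person tested is mis-specified, and the incremental ratio may be biased.

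A reader might infer that the rule necessarily overstates the incremental cost and so counts against self-testing. That is plausible if control members make more facility trips and the intervention finds more new positives, but the document does not establish it. Under assumed trip counts the error runs from -0.20t to +0.53t per extra result, and the sign depends on trip counts in both arms that are not given.

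A reader might also try to size it by letting 5-20% of the 37% uncovered controls (1,850 of an assumed 5,000 per arm) travel and test, while keeping 750 extra results. That is inconsistent. If 63% is campaign-day coverage, 92-370 later control tests cut the extra results to about 658-380 (750 - 92 and 750 - 370). If 63% is 120-day coverage, those people obtained no result at all.

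The point is worth correcting, but it is confined to the additional cost-effectiveness analysis. The primary coverage comparison and the secondary endpoints are untouched.

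**What to change.** In *Additional research within the project*, replace the ART-transport item with the participant's travel cost of obtaining the confirmed HIV test result within 120 days. It should cover, in both arms, travel for a first test after referral and travel for confirmatory testing after a reactive self-test. Leave ART travel out of the HOSENG ratio, or report it separately.

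Ask about this trip in the patient-cost sub-sample that is already planned. Apply the resulting trip cost to the facility tests identified in the study's follow-up records, including the register screening in control clusters.

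The cost is a wording change and one changed questionnaire item, with no extra participants or visits. The downside is an imprecise trip cost if few sub-sample members turn out to have tested at a facility.

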### Sample size

The sample size is driven by the VIBRA trial [22]. We assume that to achieve the VIBRA trial [22] sample size (minimum 262 HIV-positive individuals not on ART) by testing about 10,000 individuals in 100 villages, based on a previous trial [32]. According to a previous home-based HIV-testing campaign [33], we estimate an HIV-testing coverage rate of individuals aged 12 years or older in rural villages of 63%. We consider a 15% increase in coverage as relevant from a policy perspective. Using an intra-cluster correlation (ICC) of 0.028, with a sample of 100 clusters, we will require a sample size of 450 in order to have > 90% power to detect an increase in coverage rates to 78% or higher. This corresponds to an increase of 1.17 (variance inflation factor (VIF)) from the 386 individuals required in the absence of clustering. If we vary the ICC for villages and include an additional ICC for clustering at the household level [34], the maximum VIF would be 8.3 corresponding to a maximum sample size of 3204 needed to ensure 90% power to detect a 15% difference, well below the expected 10,000 individuals to be included. Table 3 displays the sample size calculations considering all relevant factors under different scenarios.

**Table 3 Tab3:** Sample size estimations for the HOme-based SElftestiNG (HOSENG) trial

Average village size	Average household size	ICC (village)	ICC (household)	VIF	Total number of clusters	Total sample size
30	2	0.028	0.05	1.04	100	402
30	2	0.028	0.1	1.07	100	413
30	2	0.05	0.05	1.20	100	462
30	2	0.05	0.1	1.34	100	518
30	2	0.1	0.05	2.95	100	1139
30	2	0.1	0.1	4.4	100	1699
30	4	0.028	0.01	1.06	100	410
30	4	0.028	0.05	1.31	100	507
30	4	0.028	0.1	1.62	100	628
30	4	0.028	0.5	4.12	100	1592
30	4	0.05	0.01	1.09	100	420
30	4	0.05	0.05	1.44	100	556
30	4	0.05	0.1	1.88	100	726
30	4	0.05	0.5	5.4	100	2085
30	4	0.1	0.01	1.15	100	442
30	4	0.1	0.05	1.73	100	668
30	4	0.1	0.1	2.46	100	950
30	4	0.1	0.5	8.3	100	3204

*ICC* intracluster correlation coefficient, *VIF* variance inflation factor

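### The planned cost per participant tested is really a cost per person with a confirmed result, and the participant cost it names arises after the endpoint

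*Protocol article*

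**What the plan says.** Under Additional research within the project, the article sets out the cost work specific to HOSENG. Direct costs cover staff, training of village health workers (VHWs), equipment, and non-medical costs to the participant. The last item is specified, after i.e., as "cost of transportation to the ART service". From these data the plan derives the "cost per participant achieving the primary endpoint within 120 days in each cluster arm", with the short name "per participant tested cost". A second, separate step is the cost-effectiveness analysis. It is tied to the primary endpoint and expressed as incremental cost per additional confirmed result, with probabilistic sensitivity analysis and acceptability curves.

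Under Endpoints, the primary endpoint is the "proportion of all individuals aged 12 years or older living in a household of the surveyed area with a confirmed HIV test result". A negative result counts if it comes from the trial's algorithm or from "being tested HIV-negative within the last 4 weeks with proof of documentation". A positive result counts if it comes from the algorithm or from "being tested HIV-positive but not yet on ART with proof of documentation, or (3) being on ART with proof of documentation".

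Under Procedure, counselors establish the HIV status of all household members and look through the health booklets at the visit. No section removes already-documented people from the cost denominator or gives a second denominator.

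**The concern.** The short name and the denominator describe different quantities. People whose status was documented before the home visit can enter the denominator although the campaign did not generate their result. A reader who takes the short name at face value, for instance to compare it with the testing cost of another programme, would be using a figure that is too low.

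The participant-cost item has a related problem. The endpoint is a confirmed test result, and travel for ART comes after it. Under Control clusters, absent or declining members are encouraged to test with the VHW or at the nearby facility. Under Intervention clusters, a person with a reactive self-test gets blood-based testing from the VHW or is referred to the facility. Travel to obtain or confirm a test is thus the participant cost that belongs to this endpoint and may differ between arms. Taken literally, the wording leaves it out.

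**Working it through.** **Inputs**
- Planned coverage p: 63% control, 78% intervention (Sample size).
- Adult HIV prevalence: 17.8% and 26.1% in the two districts (Setting).
- Share of people with HIV who know their status: 81%, a regional figure with a stated range of 64–95% (Background).
- K, the share of people aged 12 or older who meet the endpoint through documentation alone: not given, so assumed.

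**The plan's own figure.** The article states no cost figure. The coverage rates can be checked through the sample size of 386 without clustering. With a pooled-variance comparison of two proportions, two-sided alpha 0.05, power 90% and mean proportion 0.705:

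n per arm = [1.96·√(2·0.705·0.295) + 1.2816·√(0.63·0.37 + 0.78·0.22)]² / 0.15² = 192.2, rounded up to 193, so 386 in total.

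This matches. It confirms that 63% and 78% are the rates used in planning, but says nothing about K.

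**Formula.** Let C be an arm's cost and N its number of people aged 12 or older.
- Planned figure: C/(N·p)
- Cost per person tested: C/(N·(p − K))
- Relative understatement: 1 − (p − K)/p = K/p, whatever C is

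**Range for K.** If every aware person is documented, K is 17.8% × 0.81 = 14.4% to 26.1% × 0.81 = 21.1%. If only half are, K is 7.2% to 10.6%.

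| K | K/p at 63% | K/p at 78% | Cost per person tested ÷ planned figure, 63% | Same, 78% |
|---|---|---|---|---|
| 7.2% | 11.4% | 9.2% | 63/55.8 = 1.13 | 78/70.8 = 1.10 |
| 10.6% | 16.8% | 13.6% | 63/52.4 = 1.20 | 78/67.4 = 1.16 |
| 14.4% | 22.9% | 18.5% | 63/48.6 = 1.30 | 78/63.6 = 1.23 |
| 21.1% | 33.5% | 27.1% | 63/41.9 = 1.50 | 78/56.9 = 1.37 |

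**Incremental ratio.** With the same K in both arms, (0.78 − K) − (0.63 − K) = 0.15, so K cancels and the cost per additional confirmed result does not change. If K differs between arms, the two versions of the ratio part company by that difference.

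**Participant cost.** The article gives no travel cost and no number of people travelling, so no size can be computed for this part.

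**The case against.** The best defence is that the denominator is stated openly and the disputed words are only a short name placed after it. As a cost per person with a confirmed result the figure is coherent, and costing per unit of the primary outcome is a legitimate choice. That stands. It makes this a fault of labelling and of a missing companion figure. It does not make the analysis invalid.

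Three stronger readings are tempting and are not supported.
- **A biased cost-effectiveness conclusion.** The abstract and the Discussion make wider use conditional on cost-effectiveness, so a reader might infer that the conclusion is biased. It rests on the incremental ratio, which is unchanged when K is balanced, as randomization would lead one to expect.
- **Control testing made to look too cheap against the intervention.** The proportional understatement is larger in control when K is equal. However, the plan reports a cost per arm and an incremental ratio, and no ratio of the two average costs.
- **Already-documented people use no resources.** Under Intervention clusters, a kit is left for every absent or declining member aged 12 or older, and no exception for documented status is stated there. Counselor time is also spent on checking status. This affects C. It does not affect K/p.

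The size is open to challenge as well. Absent members' booklets may not be at home, the 81% is regional, and adult prevalence is applied from age 12. These points are why the range extends down to half documented. In the other direction, documented recent negatives are left out of K and would raise it. Whether the 63% already includes documented people depends on a source not shown. If it does not, control coverage on the endpoint would be 63% + K and the understatement K/(63% + K), that is 7.2/70.2 = 10.3% to 21.1/84.1 = 25.1%.

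On transport, the article refers to the VIBRA protocol for more cost detail, and the i.e. may be loose wording. That limits the point to the text as written, and does not show that the questionnaire omits test-seeking travel. Still, the item is worded as a definition and is given specifically for HOSENG.

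**Conclusion.** The point holds as a mismatch between label and denominator. The planned average is a cost per person with a confirmed result. As a cost per person tested it is understated by K/p in each arm: about 11% to 34% at 63% coverage and 9% to 27% at 78%, for an assumed K of 7% to 21%. The direction needs only K above zero. The size rests on the assumed K and on the planning coverages counting documented status as the endpoint does. The incremental ratio is not affected if K is balanced.

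The participant-cost wording is a second, separate flaw. Leaving out test-seeking travel could overstate the intervention's incremental cost if control participants travel more for testing. Some intervention participants also travel for confirmation, and the amount cannot be computed from the article. Overall severity is minor to moderate.

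**What to change.** 1. Rename the existing figure *cost per person with a confirmed result*.
2. Add a cost per person whose result was generated between the home visit and day 120, by blood test, self-test, VHW or facility test, and use the word tested only for this one.
3. Report the number of people already documented at the home visit separately, by arm. This also shows whether K is balanced.
4. Leave the incremental ratio tied to the primary endpoint, so that it stays in line with the trial's effect measure.
5. Replace or extend the participant-cost item with travel and time to obtain an HIV test, whether facility or confirmatory testing, in both arms.

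The cost is a change of wording, a split that should be available from status data collected at the visit, and one extra item in the sub-sample questionnaire. The downside is that the added unit cost will look less favourable than the planned figure.

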### Data collection and management

The campaign team will capture all data collected during the campaign using a tablet-based application and platform (MACRO, Elsevier). The randomization assignment of the villages is pre-loaded into the program and a unique household identifier is automatically generated. Before leaving the household, the completed questionnaire will be checked for mistakes and completeness. Data from the tablet devices will be uploaded regularly via secure electronic transfer and stored on a secure server at the Swiss Tropical and Public Health Institute (Swiss TPH). After the follow-up period, all confidential information of the study participants (i.e., names) will be deleted from the database and only the anonymous study ID will be kept. The informed consent forms will be stored in a secure way in the headquarter of the study center (SolidarMed Office in Butha-Buthe, Lesotho). Participant files will be maintained in storage for a period of at least 10 years after completion of the trial.

The VHWs enter data for following up the dispensed oral HIVST kits on standardized paper study forms (case report forms) that act as source documents. These data will be collected regularly by the study team and entered into the above-mentioned platform. A study data manager will monitor data quality and completeness on a weekly basis. Queries about the data will be sent to the local principal investigators for follow-up and correction, as needed. Data integrity checks will be written into the database to limit missing fields or the entry of incorrect data. The type of activity that an individual user in the online study database may undertake will be regulated by the privileges associated with their user identification code and password.

